## Abstract

**Background:**

Pregnant women were excluded from investigational trials of COVID-19 vaccines. Limited data are available to inform pregnant and postpartum women on their decisions to receive a COVID-19 vaccine.

**Methods:**

The goal of this observational, prospective cohort study is to evaluate the immunogenicity and safety of various Emergency Use Authorization (EUA) or licensed COVID-19 vaccines administered to pregnant or lactating women and describe the transplacental antibody transfer and kinetics of antibodies in mothers and infants. The study is adaptive, allowing additional groups to be added as new vaccines or vaccine regimens are authorized. Up to 20 clinical research institutions in the United States (U.S.) will be included. Approximately 200 pregnant women and 65 postpartum women will be enrolled per EUA or licensed COVID-19 vaccine formulation in the U.S. This study will include pregnant and postpartum women of all ages with and without chronic medical conditions. Their infants will be enrolled and followed beginning at birth in the pregnant cohort and beginning at the earliest possible time point in the postpartum cohort. Blood samples will be collected for immunogenicity outcomes and pregnancy and birth outcomes assessed among women and infants. Primary analyses will be descriptive and done by vaccine type and/or platform.

**Discussion:**

Given the long-standing and legitimate challenges of enrolling pregnant individuals into clinical trials early in the vaccine development pipeline, this study protocol describes our current study and provides a template to inform the collection of data for pregnant individuals receiving COVID-19 or other vaccines.

**Trial registration:**

NCT05031468.

**Supplementary Information:**

The online version contains supplementary material available at 10.1186/s12884-022-04500-w.

## Background

Pregnant women are susceptible to infection and complications from SARS-CoV-2. Observational data in the U.S. demonstrate that, while the absolute risk for severe health effects may be low, pregnant women have an increased risk of developing severe COVID-19, including illness that results in pneumonia, intensive care unit (ICU) admission, need for mechanical ventilation, and death compared with non-pregnant women of reproductive age with COVID-19 [1–5]. Pregnant women who acquire COVID-19 are more likely to experience adverse consequences including preterm birth, and their infants have an increased risk of neonatal intensive care unit (NICU) admission [2, 4, 6–9]. Maternal immunization may be a strategy to provide protection to both the mother and the infant against complications associated with COVID-19.

Several COVID-19 vaccines utilizing different platforms (e.g., mRNA, viral vectored, protein-based, inactivated virus), are available or will soon be available under EUA in the U.S. or will soon be licensed. Pregnant women were not included in pivotal efficacy trials of these vaccines, and currently, only the Pfizer/BioNTech mRNA vaccine is being tested in a randomized controlled trial among pregnant women [10]. Conducting placebo-controlled trials in pregnant women is increasingly problematic given the widespread availability of these vaccines in the U.S. and many other countries, where approved vaccines are being administered to individuals who are pregnant or postpartum, as part of national vaccination campaigns. Safety data are being collected through various surveillance systems in the U.S., with reassuring results to date [11, 12]. However, many knowledge gaps remain regarding the use of COVID-19 vaccines during pregnancy and after delivery. Data on kinetics and durability of maternal antibodies, transplacental antibody transfer to the infant, breast milk antibodies, and kinetics of antibodies in infants, are limited [13, 14].

We designed an observational study in pregnant and postpartum women in order to fill knowledge gaps on use of COVID-19 vaccines in these populations. The purpose of this manuscript is to share our rationale and study design, laboratory evaluations, and analyses plans, and to serve as a template for similar studies of COVID-19 and other vaccines in pregnant and postpartum populations (including those who are lactating). It is expected that the results of this study will inform policy recommendations and personal decision-making on the use of approved COVID-19 vaccines in pregnant and postpartum individuals in the U.S. and globally.

### Trial overview

The goal of this observational, prospective cohort study is to evaluate the immunogenicity and safety of various EUA or licensed COVID-19 vaccines administered to pregnant or lactating women and describe the transplacental antibody transfer and kinetics of antibodies in mothers and infants. The adaptive study design allows the evaluation of up to 5 vaccines, with groups added as new vaccines are authorized and vaccination recommendations evolve.

## Methods

Approximately 1000 total study participants who receive or plan to receive a COVID-19 vaccine during pregnancy and/or postpartum and their infants will be enrolled. Pregnant women during any trimester of pregnancy will be enrolled either prior to or after receipt of vaccine(s) and followed with periodic blood draws for immunogenicity assessments. Pregnancy status will be confirmed through medical records, and vaccination status will be confirmed through medical records or vaccination card. Infants will be enrolled at birth. At that time, maternal and cord blood samples will be obtained, and details of the birth will be collected. Mother and infants will be followed through 12 months with periodic immunogenicity sampling and safety follow-up. Thus, the study duration of participation for pregnant women will be up to 20 months. A cohort of postpartum women will be enrolled either prior to or after receipt of vaccine(s) within the first 2 months of delivery. Their infants will be enrolled at the same time and will be followed through 12 months with periodic immunogenicity sampling and safety follow-up. A schedule of events is found in Tables 1 and 2.

**Table 1 Tab1:**
[figure not shown]
Schedule of Events for Multi-site Observational Maternal and Infant COVID-19 Vaccine Study (MOMI-Vax). Schedule of Events: Pregnant Women and their Infants^a^

*Abbreviations*: *mL* milliliters

^a^*n* = approximately 200 pregnant women who are scheduled to receive or have completed any licensed or EUA COVID-19 vaccine series per vaccine type and approximately 200 infants born to pregnant women per vaccine type

^b^Only applicable if V01 was completed pre-vaccination

**Table 2 Tab2:**
[figure not shown]
Schedule of Events for Multi-site Observational Maternal and Infant COVID-19 Vaccine Study (MOMI-Vax). Schedule of Events: Postpartum Women and their Infants^a^

*Abrreviations*: *mL* milliliters

^a^*n* = approximately 65 postpartum women who are scheduled to receive or have initiated any licensed or EUA COVID-19 vaccine series within first 2 months of delivery; *n* = approximately 65 infants of postpartum women

^b^For mothers vaccinated prior to enrollment: Document COVID-19 vaccination date(s) and type

^c^Optional, for mothers enrolled at delivery

^d^If visit overlaps with Visit 101 (i.e., mother received full series prior to enrollment), the two visits will be combined

Written informed consent will be obtained from the pregnant and postpartum participants at the enrollment visit. Informed consent will be obtained from the mother for the infant either at the time of birth or for postpartum individuals, at time of enrollment (see Additional Files 1, 2 and 3). This study will be carried out in accordance with Good Clinical Practice (GCP) guidelines. The Vanderbilt University Medicine Center Institutional Review Board (IRB) has reviewed and approved this protocol, consent forms and associated documents. Each institution engaged in this research will hold an Office of Human Research Protections (OHRP)-approved Federal Wide Assurance (FWA). All study records will be kept in a locked file cabinet or maintained in a locked room at the site. Electronic files will be password-protected. Only people who are involved in the conduct, oversight, monitoring, or auditing of this study will be allowed access to the PHI that is collected. Any publications from this study will not use information that will identify subjects by name. Organizations that may inspect and/or copy research records maintained at the site for quality assurance (QA) and data analysis include groups such as the local or central IRB, NIAID, and the FDA.

Quality oversight procedures will be implemented by FHI 360 in consultation with the Infectious Disease Clinical Research Consortium (IDCRC) Clinical Operations Unit (COU). Quality oversight will include review of each participating site’s Clinical Quality Management Plan - Quality Management Summary Report on a quarterly basis, as well as overall enrollment tracking and oversight of performance trends.

### Study population

This observational study was designed to be broadly inclusive to reflect the need to collect information on pregnant and postpartum women of all ages, with and without chronic medical conditions, and with singleton or multiple gestations. The study will include postpartum women whether or not they choose to breastfeed. The exclusion criteria are limited to behavioral or cognitive impairment, psychiatric disease or any condition that might pose a health risk and interfere with the individual’s ability to participate and/or the evaluation of study objectives (Table 3).

**Table 3 Tab3:** Study Inclusion and Exclusion Criteria

**Inclusion Criteria**	Pregnant Women 1. Pregnant individuals scheduled to receive or have received complete vaccination series of any licensed or EUA COVID-19 vaccine^a^ 2. Willing and able to provide consent for study participation for herself and for her infant prior to initiation of any study procedures.
	Postpartum Women 3. Individuals scheduled to receive or who have initiated vaccination series of any licensed or EUA COVID-19 vaccine within the first 2 months postpartum^b^ 4. Willing and able to provide consent for study participation for herself and for her infant prior to initiation of any study procedures (a separate consent form will be used for their infants).
	All participants 5. Understands and agrees to comply with all study procedures. 6. Agrees to sign medical release for herself and her infant to allow study staff to gather pertinent medical information, pregnancy outcome data, and medical information as needed.
**Exclusion Criteria**	1. Behavioral^c^ or cognitive impairment or psychiatric disease that, in the opinion of the investigator, may interfere with the participant’s ability to participate in the study. 2. Any condition which, in the opinion of the investigators, may pose a health risk to the participant or interferes with the evaluation of the study objectives

*Abbreviations*: *EUA* Emergency Use Authorization

^a^No limitation on age of mother, health status, or gestational age at enrollment

^b^No limitation on maternal age or health status

^c^Includes having a history of alcohol or drug abuse within 1 year prior to study enrollment

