### Enrollment

Screening and enrollment visits will occur sequentially or on the same day. Study staff will collect baseline information on participants (e.g., demographics, medical history, obstetric history, history of respiratory illnesses) (Tables 1 and 2). Pregnant individuals who meet all eligibility criteria will be enrolled. Infants born to pregnant individuals will become study participants upon delivery and maternal consent. Postpartum individuals who meet all eligibility criteria will be enrolled along with their infants. Once enrolled, each individual will be registered in a study database. Enrollment will continue until number of participants is reached for a particular vaccine type/study group. If new vaccines receive EUA or licensure, vaccine types will be added.

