**Fig. 1 Fig1:**
[figure not shown]
Sample Size Calculation based on Width of 95% Confidence Intervals for Neutralizing Antibodies for COVID-19 Vaccines included in MOMI-Vax. Legend: The curve shows neutralizing antibody from Phase 1 studies and demonstrates the inflection point for sample size at approximately 150 individuals per group, with little gain in precision with higher samples sizes. Results similar using binding antibody data (results not shown)

The analysis groups are:Group 1: Individuals who receive a COVID-19 vaccine during pregnancy (up to 200 individuals per vaccine type).Group 2: Individuals who receive a COVID-19 vaccine postpartum (up to 65 individuals per vaccine type).Group 3: Infants of individuals who receive COVID-19 vaccine during pregnancy (approximately 200 infants per vaccine type).Group 4: Infants of individuals who receive COVID-19 vaccine postpartum (approximately 65 infants per vaccine type).Group 5: Individuals who receive additional COVID-19 vaccine(s) (booster) during pregnancy (up to 200 individuals).Group 6: Infants of individuals who received additional COVID-19 vaccine(s) (booster) during pregnancy (approximately 200 infants).

The study will not randomize participants between vaccines, and statistical analyses will seek to adjust for covariates when deemed appropriate to account for potential confounders. All analyses will be done by vaccine type and/or platform or vaccination regimen on all available data, and analyses for each endpoint are outlined in Table 5. Multiple imputation may be used if there is substantial missingness. Additional analysis details will be included in a statistical analysis plan.

**Table 5 Tab5:** Primary, Secondary and Exploratory Objectives, Endpoints and Analyses

	Objectives	Endpoints	Analyses
**Primary**	1. Immunogenicity: To describe kinetics and durability of maternal serum antibodies following receipt of COVID-19 vaccine in individuals vaccinated during pregnancy, by vaccine type and platform.	• Geometric Mean Titer (GMT) of serum immunoglobulin G (IgG) enzyme-linked immunosorbent assay (ELISA) and neutralizing (Neut) antibodies after vaccination and up to 12 months after delivery, by vaccine type and platform^a^	• Geometric Mean Titers (GMTs) and 95% Confidence Intervals (CIs) will be calculated in Group 1. Plots such as reverse cumulative distributions or longitudinal presentations of GMTs will be presented.

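### Inclusion criterion 1 does not require a dose in the current pregnancy, so a woman vaccinated only before conception can be enrolled although no analysis group holds her

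*Protocol article*

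**What the plan says.** **Entry.** Criterion 1 for pregnant women (Study population, Table 3) is "Pregnant individuals scheduled to receive or have received complete vaccination series of any licensed or EUA COVID-19 vaccine". Its footnote adds only "No limitation on age of mother, health status, or gestational age at enrollment". The postpartum criterion in the same table does carry a window: "Individuals scheduled to receive or who have initiated vaccination series of any licensed or EUA COVID-19 vaccine within the first 2 months postpartum".

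**Target.** Table 1 footnote a sets the number as "approximately 200 pregnant women who are scheduled to receive or have completed any licensed or EUA COVID-19 vaccine series per vaccine type".

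**Enrolment.** The Enrollment section says that pregnant women who satisfy all criteria are enrolled. It closes recruitment by this rule: "Enrollment will continue until number of participants is reached for a particular vaccine type/study group".

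**Intended population.** The opening paragraph of Methods describes participants as those "who receive or plan to receive a COVID-19 vaccine during pregnancy and/or postpartum".

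**Analysis groups.** The list in Statistics begins "Group 1: Individuals who receive a COVID-19 vaccine during pregnancy (up to 200 individuals per vaccine type"; the bracket closes there. Group 5 requires a booster in pregnancy, up to 200 women, with no multiplication by vaccine type. Groups 3 and 6 are the corresponding infants. Groups 2 and 4 are women vaccinated postpartum and their infants.

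**Version.** Trial status says the article reflects Protocol Version 1.0 together with the amendment that added the pregnancy booster group.

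**The concern.** The entry rule and the analysis groups describe different women. The rule asks whether she is pregnant now and has a series planned or finished. The groups ask whether a dose fell in pregnancy. A woman who finished her series before conceiving, with no later dose, passes the first test and fails the second.

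All three primary objectives in Table 5 concern women vaccinated in pregnancy or their infants. A woman without such a dose contributes to none of them. She also has no trimester of vaccination for secondary objectives 3 and 4. If she occupies one of the roughly 200 places, Groups 1 and 3 end up smaller than planned after recruitment for that vaccine has closed.

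The booster amendment widens the gap. A woman intended for Group 5 enters through her completed primary series. So does a woman with the same series and no booster. Nothing in criterion 1 separates them.

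**Working it through.** **Step 1: trace one woman through the text.** Take a woman who is pregnant at enrolment, completed her series before conception and receives no dose in pregnancy.

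| Place in the article | Result |
|---|---|
| Table 3, criterion 1 | Eligible: series complete, no date condition |
| Table 3, footnote to criterion 1 | No timing added |
| Enrollment | Enrolled, since she meets the criteria |
| Table 1, footnote a | Fits the wording of the target of about 200 |
| Methods, opening paragraph | Outside the described population, unless later vaccinated postpartum |
| Statistics, Group 1 | Not a member: no dose in pregnancy |
| Statistics, Group 5 | Not a member: no booster in pregnancy |
| Statistics, Group 2 | Not a member, unless vaccinated postpartum |

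She can be enrolled and belongs to no group.

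**Step 2: could such women present?** The Discussion places permissive use of the vaccines in pregnancy in late 2020. Trial status gives recruitment from July 2021 to an expected March 2022. Mid-December 2020 (assumed) to mid-March 2022 is about 15 months, which is longer than a pregnancy. A series completed before conception was therefore possible, increasingly so as recruitment went on. The article gives no counts, so the share is unknown.

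**Step 3: how are places counted?** Table 1 footnote a ties the target to the wording of criterion 1. The Enrollment section counts by vaccine type/study group. Under the first reading she uses a place; under the second she does not. For a woman enrolled before vaccination, membership of Group 1 or 5 is not yet known at entry, so a count made at enrolment cannot apply the group definition to her.

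**Step 4: effect on precision, illustration only.** The plan's 200 and its inflection at about 150 cannot be reproduced: the standard deviations come from cited Phase 1 data and Fig. 1 is not shown. Neither figure is challenged here.

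Let f be the share of the 200 places used by women outside the group (assumed, 0 to 50%).

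- Analysable number: n = 200 × (1 − f).
- Log-scale 95% half-width: t(0.975, n − 1) × SD / √n.
- The ratio to the half-width at n = 200 does not depend on the SD.
- Enrolment needed to keep 200 analysable: 200 / (1 − f), rounded up.

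At n = 200: 1.972/√200 = 0.1394. At n = 150: 1.976/√150 = 0.1613, ratio 1.157. At n = 100: 1.984/√100 = 0.1984, ratio 1.423.

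| f | n | Half-width relative to n = 200 | Enrolment needed for 200 |
|---|---|---|---|
| 10% | 180 | 1.055 | 223 |
| 20% | 160 | 1.120 | 250 |
| 25% | 150 | 1.157 | 267 |
| 30% | 140 | 1.198 | 286 |
| 50% | 100 | 1.423 | 400 |

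For an assumed SD of log10 titer from 0.3 to 0.6, the geometric mean is known to within a factor of 1.101 to 1.212 at n = 200, 1.118 to 1.250 at n = 150, and 1.147 to 1.315 at n = 100.

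**The case against.** The case against is substantial, and much of it stands.

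- **Counting by study group.** The Enrollment section names the study group. If sites apply the group definitions, a woman with only pre-conception doses uses no Group 1 place. This stands as one reading; Table 1 footnote a supports the other. A reader might infer that such women were enrolled and did fill the quota. The article does not show that.
- **Contaminated primary estimates.** A reader might fear that pre-conception titers and cord-to-maternal ratios are pooled into the primary results. Table 5 computes those in Groups 1 and 3, which are defined by vaccination in pregnancy, and vaccination dates are collected. Pooling would mean ignoring the plan's own definitions, so the document does not support this.
- **The Methods statement.** It already describes the narrower population. That helps a careful site, but it contradicts Table 3 rather than amending it, and Table 3 is what determines eligibility.
- **Women vaccinated after delivery.** It is tempting to say that they too have no group. Group 2 can hold them. Women scheduled but never vaccinated are ordinary attrition.
- **Boosters.** Group 5 women are not shut out, because a completed series satisfies criterion 1. Assigning groups later from vaccination dates is acceptable in a descriptive cohort. What remains is that the criterion does not require the booster to fall in pregnancy.
- **Precision.** The legend to Fig. 1 sees little gain above about 150 per group, so losing up to 25% of places costs little by the plan's own standard.

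**Conclusion.** The point holds as an inconsistency between the eligibility rule and the analysis population. Criterion 1 and Table 1 footnote a admit women whom no analysis group holds, contrary to the Methods description, the definitions of Groups 1 and 5, and the primary objectives. This is a stated rule that admits the wrong women, not a detail left to the analysis plan.

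The consequence is a risk of lost places, and its size cannot be derived from the article. Deriving a share from calendar dates is tempting, but it would need uniform vaccination dates, a fixed gestation at entry and a known mix of entrants, none of which the article gives. The calculation therefore shows only what a given share would cost: about 16% wider log-scale intervals at 25%, and about 42% wider at 50%. It assumes that women outside the group count towards the 200 and are then left out of the analysis. The figure of 200 per vaccine type is that of Group 1; Group 5 has up to 200 in all.

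It should be fixed, but it does not undermine the primary analyses as defined.

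**What to change.** 1. Reword criterion 1 and Table 1 footnote a to agree with Methods and the group list. Require at least one primary-series dose (Group 1) or additional dose (Group 5), received in the current pregnancy or scheduled before delivery.
2. Count a woman towards her group's target only once that dose is documented. This also deals with women who are scheduled but not vaccinated before delivery.
3. Analyse any woman already enrolled without a dose in pregnancy, and her infant, outside Groups 1, 3, 5 and 6. If she is vaccinated postpartum within the window already stated, place the pair in Groups 2 and 4.

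The cost is one eligibility amendment, with some women turned away or replaced. No new data are needed: Methods already confirms pregnancy and vaccination status from records or the vaccination card, and Follow-up already collects vaccination dates.

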## Study procedures

### Recruitment and screening

Participants will be recruited from up to 20 academic affiliated, IDCRC sites throughout the U.S. Study staff will inform potential participants/legally authorized representatives of the study, obtain informed consent, and determine study eligibility.

